## Abstract

**Background:**

Currently, primary care for frail older people is reactive, time consuming and does not meet patients' needs. A transition is needed towards proactive and integrated care, so that daily functioning and a good quality of life can be preserved. To work towards these goals, two interventions were developed to enhance the care of frail older patients in general practice: a screening and monitoring intervention using routine healthcare data (U-PRIM) and a nurse-led multidisciplinary intervention program (U-CARE). The U-PROFIT trial was designed to evaluate the effectiveness of these interventions. The aim of this paper is to describe the U-PROFIT trial design and to discuss methodological issues and challenges.

**Methods/Design:**

The effectiveness of U-PRIM and U-CARE is being tested in a three-armed, cluster randomized trial in 58 general practices in the Netherlands, with approximately 5000 elderly individuals expected to participate. The primary outcome is the effect on activities of daily living as measured with the Katz ADL index. Secondary outcomes are quality of life, mortality, nursing home admission, emergency department and out-of-hours General Practice (GP), surgery visits, and caregiver burden.

**Discussion:**

In a large, pragmatic trial conducted in daily clinical practice with frail older patients, several challenges and methodological issues will occur. Recruitment and retention of patients and feasibility of the interventions are important issues. To enable broad generalizability of results, careful choices of the design and outcome measures are required. Taking this into account, the U-PROFIT trial aims to provide robust evidence for a structured and integrated approach to provide care for frail older people in primary care.

**Trial registration:**

NTR2288

## Background

With an increasing number of older people in society, the number of frail older people with complex care needs will rise [1]. Frailty is a term often used among health care professionals to characterize older people who have a functional loss of resources in different domains. Frail older people have an increased risk for adverse health outcomes, such as mortality, morbidity and institutionalization [2-5]. The increasing number of frail older people will seriously challenge the health care system because primary care for these patients is currently fragmented, time consuming and reactive [6]. Because the care system does not address their needs, many older patients and their caregivers have a poor quality of life [7,8]. To preserve functional performance and maintain independent living in this vulnerable population, a transition is needed towards more proactive, integrated and structured health care for older people.

Until today, scientific evidence on how primary care providers can provide optimal care for frail older people with complex care needs is inconsistent. Previous intervention studies often used a selection of patients at risk combined with an additional geriatric assessment and follow-up visits [9,10]. However, evidence for these complex interventions is not clear. Moreover, it is unclear what the independent effectiveness of these interventions is.

One widely studied approach to select patients at risk is panel management. Panel management involves periodic reporting of clustered electronic medical record data from a certain 'patient panel' as an overview of the most important health parameters [11,12]. Missed patient encounters and care gaps can then easily be identified, which enables proactive, integrated and timesaving care. Panel management programs have been set up for various chronic diseases; however, integrated panel management approaches for frail older patients are lacking [13].

Other solutions to prevent functional decline are complex interventions, such as preventive home visiting programs with comprehensive geriatric assessments [9,14-16]. Little is known about the effectiveness of the different interacting components of these complex interventions. Elements that were demonstrated to be promising in different intervention studies are a multidisciplinary, multifactorial approach with tailor-made interventions and an individual assessment for frail older people provided by a (primary) care team with long-term follow-up [17-19].

To understand the effectiveness of these different approaches, we developed two interventions: a screening and monitoring intervention using routine healthcare data with the Utrecht Periodic Risk Identification and Monitoring system (U-PRIM) and a nurse-led multidisciplinary intervention program, U-CARE. In the **U**trecht **P**rimary care P**RO**active **F**railty **I**ntervention **T**rial (U-PROFIT), the effectiveness of the U-PRIM intervention, alone and in combination with U-CARE, will be assessed in comparison to usual care. The aim is to preserve physical functioning and improve quality of life for frail older people and their caregivers. The trial will be conducted from October 2010 to spring 2012. The aim of this paper is to describe the design of the U-PROFIT trial, the content of the two interventions and its methodological challenges.

## Methods

### Design and setting

A single-blind, three-armed, cluster-randomized controlled trial with a one-year follow-up is being conducted (see Figure 1). Recruitment was performed in three primary care networks with almost 70 practices in Utrecht, the Netherlands.

**Figure 1 F1:**
[figure not shown]
**Flowchart**.

### Participants

#### Inclusion criteria

Selection of patients is performed by the U-PRIM system, a software application that is installed in all participating general practices. Exploring the electronic medical records (EMRs) in each general practice, U-PRIM will screen for three inclusion criteria in patients aged 60 years or older:

- Multimorbidity (defined as a frailty index score of ≥ 0.20; see the 'U-PRIM intervention' section)

- AND/OR

- Polypharmacy (defined as the chronic use of five or more different medications) [20]

- AND/OR

- Care gap in primary care of three or more years (defined as not having consulted the GP in the past three years, except for the yearly influenza vaccination).

#### Exclusion criteria

Terminally ill patients or patients living in an elderly home or nursing home are excluded. Reasons for exclusion are registered on the general practice level.

### Procedure

At the start of the inclusion period, U-PRIM automatically generates a list of frail patients of 60 years and older in every participating practice. Using the U-PRIM software, data extractions from the electronic medical records (EMRs) in the practices are uploaded to an external server area. Here, reports on frail patients are generated and delivered back to the general practice. To guarantee patient privacy, U-PRIM software encodes the personal data by means of a third trusted party procedure, so personal data are only disclosed to the general practice personnel.

Eligible patients are listed in the first U-PRIM report. These patients are approached by their GP with a patient information letter and informed consent form for participation in the U-PROFIT trial. In addition, patients are asked if they have an informal caregiver. If so, the caregiver is also invited to participate in the study to investigate caregiver burden.

In the practices in the control group, a similar U-PRIM report with potentially frail patients is generated, but this report is not visible to the GP.

### Ethical considerations

The U-PROFIT trial is approved by the Institutional Review Board of the University Medical Center Utrecht (UMCU) with protocol ID 10-149/O and registered in the Netherlands Trial Register: NTR2288.

### Randomization and blinding

The participating general practices are randomly allocated to one of the two intervention groups (A or B) or the control group (C) by cluster randomization on the general practice level (see flowchart). Practices in group A are allocated to the U-PRIM intervention, those in group B to the U-PRIM plus U-CARE intervention and the practices in group C formed the control group. Within the 58 participating general practices, clusters are created because some general practices are working closely together at the same location. Before randomization, clusters are stratified according to the expected number of frail older people in the general practice. The cluster size is estimated based on the number of invitations for the yearly influenza vaccination per practice.

### Blinding

#### Informed consent

A modified informed consent procedure is used to maintain a single-blind design; the so- called "consent to postponed information" [21,22]. With this procedure, a valid assessment of subjective outcomes can be obtained in a trial even if the patients cannot be blinded to the intervention. Additionally, selection bias and dropout in the control group can be reduced. In the U-PROFIT trial, patients were not informed as to which intervention group their general practice was allocated until the end of the follow-up period.

### Blinding of the GPs and practice nurses

Blinding the GPs and their practice nurses is not possible in this study because they are part of the intervention.

### Blinding the investigators

Because the investigators need to directly communicate with the general practices about the study, it is not possible to blind the investigators. However, during data analysis, investigators will be blinded to the data. When the data analysis is completed, this information will be disclosed to the investigators.

### The interventions

Two interventions are being tested in the U-PROFIT trial: 1. Screening and Monitoring of frailty (U-PRIM) and 2. Nurse-led multidisciplinary intervention program (U-CARE).

### Intervention 1: U-PRIM

The U-PRIM software application is an electronic monitoring system aiming at identification of older patients at increased risk of frailty in routine health care data. The software is based on periodic screening for relevant risk factors in the EMRs of the general practice.

U-PRIM screens for three core risk factors in patients aged 60 years or older. These are also the eligibility criteria of the U-PROFIT trial as described earlier (multimorbidity, polypharmacy and a care gap).

### Multimorbidity

The frailty index concept is used as an indicator of multimorbidity [23]. The frailty index uses 50 so-called 'health deficits': symptoms, signs, diseases, social problems and functional impairments, all routinely encoded in the EMR using International Classification of Primary Care (ICPC) codes (see Additional file 1). In the choice of the deficits, we followed previously published guidelines for the construction of a frailty index [24].

U-PRIM assesses the number of deficits in each individual. The frailty index score expresses the number of deficits present as a proportion of the total number of deficits [25]. Thus, a patent with 15 deficits has a frailty index score of 0.30 (15/50). For this study, multimorbidity based on the frailty index alone is defined as a frailty index score of ≥ 0.20 [26].

### Polypharmacy

The U-PRIM software screens the medication list for chronic drug use, using anatomical therapeutic chemical (ATC) codes. Chronic use is present when the medication was prescribed at least three times in the past year, with at least one prescription in the last six months. Polypharmacy is in this study is defined as 5 or more different drugs in chronic use in the past year [20].

### Care gap

The period that patients are out of sight of their GP is assessed to include possible care avoiders prone to self-neglect, for example patients with dementia, psychiatric conditions or alcohol abuse [27]. For this study, a "care gap" is defined as a period of at least 3 years without GP consultation, excluding the annual influenza vaccination.

### The U-PRIM procedure

In the U-PROFIT trial, the periodic U-PRIM frailty screening of the trial population takes place every three months in intervention groups A and B. This results in a U-PRIM report for each general practice with a selection of older patients at high risk of adverse health outcomes. Patients are prioritized by means of the frailty index score, with possibilities to prioritize according to polypharmacy or care gap. For an example of a U-PRIM report, see Additional file 2.

The report will be passed on to the GP in intervention groups A and B. In group A, GPs are asked to act upon the U-PRIM report in accordance with current available guidelines and best practices and to carry out interventions among the frail elderly patients if needed. In group B, all patients selected by U-PRIM will receive the additional steps of the U-CARE program (see intervention 2). In every participating practice in group A and B, a staff member is responsible for generating the reports with the U-PRIM computer program and for distributing the report among the care providers involved. These contact persons received protocolized, one-on-one guidance with the first U-PRIM report, with an explanation of the software application and suggestions on how to implement the report in daily clinical practice.

### Intervention 2: U-CARE program

U-CARE is a nurse-led, multidisciplinary intervention program to be used in frail patients selected by U-PRIM. Specially trained, registered practice nurses provide structured and integrated care based on a patients' needs approach.

U-CARE is developed by a multidisciplinary team consisting of researchers and practitioners in nursing and primary care medicine. Three experienced practice nurses, a panel of experts and a panel of older people are involved to validate the content.

The program consists of three steps. The first step is a frailty assessment for patients at risk. The second step is a comprehensive geriatric assessment (CGA) at home of frail patients. The third step is a tailor-made care plan with evidence-based interventions developed by the practice nurse. Details of the development and the content of the program are described elsewhere [[name] et al: Development of a nurse-led multidisciplinary intervention program (U-CARE) to prevent functional decline in frail older people in primary care, Unpublished].

### Step 1. Frailty assessment

The level of frailty in patients at risk selected by U-PRIM will be further explored with the Groningen Frailty Indicator questionnaire (GFI). The GFI is a 15-item validated questionnaire that assesses frailty from a functional ADL/IADL perspective on four domains: physical, cognitive, social and psychological [28]. Scores on each item are zero or one, and the total score ranges from 0 (not frail) to 15 (severely frail). We chose a score of 4 or higher as the relevant cut-off [29] for the selection of patients that should be visited for a comprehensive geriatric assessment. The GFI has shown high internal consistency and construct validity [30]. This questionnaire will be sent to all patients selected by U-PRIM.

The INTERMED for the Elderly (IM-E) [31] and the Groningen Wellbeing Indicator (GWI) are additional assessments included in U-CARE to enable a multidimensional approach and to measure patients' needs and complexity of care among frail patients on the GFI.

### Step 2. Comprehensive Geriatric Assessment at home (CGA)

For those patients identified as being frail, a CGA at home is conducted by a registered practice nurse. During this home visit, the practice nurse focuses on patients' health problems and needs in a structured manner based on the outcome of the frailty assessment. Based on the literature and their prevalence [32-34], ten health problems in older patients with additional assessments are included in the CGA (see Additional file 3).

### Step 3. Tailor-made care plan

In collaboration with the GP, the practice nurse will prepare a tailor-made care plan based on the outcome of step 2. This tailor-made care plan consists of interventions derived from evidence-based care plans developed by the research team, practice nurses and experts. For all ten health problems assessed in the CGA, separate evidence-based care plans are developed. The use of the care plan ensures uniformity among practice nurses in tailoring and delivering interventions per health problem. Flowcharts with suggested (nursing) interventions per health problem are developed as a practical tool and will help to guide the practice nurses through a structured process of decision making.

### Training program

All practice nurses will receive an extended U-CARE training program that consists of 5 weeks of 4 hours of lessons in class and 4 hours of self-study. During this training program, the included frailty assessments, the content of the CGA and the evidence-based care plans will be discussed. The U-CARE training program is set up in collaboration with the University of Applied Science Utrecht in the Netherlands.

One month prior to the start of the trial, all GPs and registered practice nurses from intervention group are participating in a training session of 4 hours in which the content of U-CARE program is explained and discussed. Additionally, a workshop about collaboration between GP's and practice nurses is set up.

### Outcomes and measurements

#### Primary outcome

The primary outcome of the U-PROFIT trial is the level of Activities of Daily Living (ADL) as measured with the Katz ADL index score [35]. The Katz index measures independence of ADL on six items (bathing, dressing, toileting, transferring, eating and the use of incontinence materials). The score ranges from 0 (total independence) to 6 (total dependence), and it is widely used to assess activities of daily living [36]. Baseline ADL functioning (T0) will be compared with ADL functioning after six months (T1) and one year of follow-up (T2). The questionnaire will be filled in by the patient or a proxy relative.

#### Secondary outcomes

Secondary outcome parameters will be measured at the same time as the primary outcome parameter (T0-T1-T2).

1. Quality of life will be measured with RAND-36 and EuroQol (EQ-5D) [37,38]

2. Mortality

3. Number of nursing home admissions

4. Number of emergency department and out-of-hours GP surgery visits

5. Caregiver burden measured with Self-Rated Burden (VAS) and Carer-Qol [39]

### Additional data collection

Routine health care data will be extracted from the EMRs of the participating practices. Socio-demographic data, such as age, gender, educational level, ethnicity, marital status and living situation, will be gathered at baseline. General practice characteristics, such as size, percentage of older people, working experiences and geographical location of the general practice, will also be gathered.

### Process evaluation

To understand the different components, their interaction and the applicability of the U-CARE program, a feasibility study will be conducted among doctors and practice nurses of intervention group B. Furthermore, interventions delivered by the practice nurse or other health care providers will be registered to gain insight into targeted interventions that are performed by the practice nurses.

The U-PRIM system will be evaluated on psychometric properties, prognostic value for adverse health outcomes and in concordance with the GFI, and the system will be refined following a user demands study.

In addition, qualitative data on patients' satisfaction with the U-CARE program will be qualitatively assessed. In the end, various data will be collected to perform a cost-effectiveness analysis, e.g., data on workload of the GP and practice nurses and time registration.

### Sample size calculation

At present, a valid estimation of the variance in the KATZ ADL results within and between general practices cannot be given because these data are not available for Dutch populations. For that reason, a formal power analysis for the cluster-randomized trial is not possible. Therefore, it is also not feasible in this study to take into account a potential cluster effect. In line with Faber et al., [40] we assume that any randomization effect per practice will be absent. Furthermore, we assume that with an expected number of at least 5000 frail older people included, relevant effects can be found on the outcome between the clusters because the power of a trial increases if the number of clusters, subjects, or repeated measures within a subject increases.

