### Design

As mentioned, the two interventions are tested and embedded in routine clinical practice. Therefore, it s hard to create controlled experimental circumstances. We randomized on a practice level, and some practices may have already use screening lists or structured plans to provide care for older people, while others have not. In addition, in some practices, a practice nurse may have already been part of the practice team. Because all practices can be randomized in one of the intervention groups or in the control group, we consider these differences in elderly care at baseline as normal variations in clinical practice. In this way, both interventions are compared to the broad range of routine clinical care, enabling generalizability.

We chose a three-armed design for several reasons. First, our baseline assumption is that the U-PRIM screening followed by usual care and the combination of U-PRIM and U-CARE will both give better results than current usual care. Additionally, we hypothesize that both interventions are synergistic and that the effect of U-PRIM and U-CARE is more effective than the U-PRIM intervention alone [41].

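### The sample-size section treats an unknown practice effect as absent and asserts that 5000 patients suffice; the claim is unsupported and overstates sensitivity for any ICC above zero

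*Protocol article*

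**What the plan says.** The Abstract (Methods/Design) describes a "three-armed, cluster randomized trial in 58 general practices in the Netherlands" and puts expected enrolment at about 5000. Randomization and blinding adds that "clusters are created because some general practices are working closely together at the same location", so the units randomised number fewer than 58; how many fewer is not stated.

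The Sample size calculation section starts from the fact that no valid estimate of the Katz variance within and between Dutch practices is available. It draws three consequences:

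- No formal power calculation can be made.
- Clustering cannot be allowed for: "Therefore, it is also not feasible in this study to take into account a potential cluster effect".
- Citing an outside study, "we assume that any randomization effect per practice will be absent".

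It then assumes that "with an expected number of at least 5000 frail older people included, relevant effects can be found on the outcome between the clusters", on the ground that power grows with more clusters, subjects or repeated measures. No significance level, power, target difference, SD, ICC or design effect is given.

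Two Discussion sections bear on the assumption. Design notes that "some practices may have already use screening lists or structured plans to provide care for older people, while others have not", and that only some practices may already have a practice nurse. Feasibility and adherence says effectiveness may vary with the characteristics of the professionals.

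**The concern.** An unknown variance component calls for a range of plausible values. Setting it to zero is the most favourable choice available, and the section offers no evidence for it beyond the citation. It is also implausible on the article's own account: practices that differ in how they organise care for older people are unlikely to have identical mean Katz scores.

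The general remark about power does not rescue the figure of 5000. Adding patients to a fixed set of clusters brings diminishing returns and then almost none.

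This paragraph is the article's only sample-size basis for the primary outcome, covering each intervention against usual care and the combined intervention against U-PRIM alone. If its claim is taken at face value, a null pairwise result could be read as excluding a relevant effect when the trial could not have detected it reliably.

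**Working it through.** **The plan's own figure.** The 5000 cannot be reproduced. It is an expected recruitment number with no significance level, power, difference or SD attached. What can be computed is the sensitivity it implies with and without clustering.

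**Inputs from the article.** N = 5000; three arms; 58 practices.

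**Assumptions made here.** Equal arms, so 5000/3 = 1667 per arm; 58 equal clusters, so m = 5000/58 = 86.2; two-sided 5%; 80% power; effects in SD units; no dropout; no gain from covariates or repeated measures; ICC from 0 to 0.05.

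**Formulas.**

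- Design effect: DE = 1 + (m − 1) × ICC
- Effective total N = 5000/DE
- Standard error of a pairwise difference: SE = √(2 × DE/1667)
- Detectable difference = (1.960 + 0.842) × SE
- Power at difference d = Φ(d/SE − 1.960)

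Example at ICC 0.02: DE = 1 + 85.2 × 0.02 = 2.70; effective N = 1849; SE = √(2 × 2.70/1667) = 0.0570; detectable difference = 2.802 × 0.0570 = 0.160 SD.

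| ICC | DE | Effective N | Detectable difference (SD) | Ratio to ICC 0 (√DE) | Power at 0.10 SD | Power at 0.20 SD |
|---|---|---|---|---|---|---|
| 0 | 1.00 | 5000 | 0.097 | 1.00 | 82% | >99% |
| 0.005 | 1.43 | 3506 | 0.116 | 1.19 | 68% | >99% |
| 0.01 | 1.85 | 2700 | 0.132 | 1.36 | 56% | 99% |
| 0.02 | 2.70 | 1849 | 0.160 | 1.64 | 42% | 94% |
| 0.05 | 5.26 | 951 | 0.223 | 2.29 | 24% | 71% |

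**Ceiling from the fixed number of clusters.** As m grows, effective N tends to (number of clusters)/ICC. With 58 clusters that is 5800 at ICC 0.01, 2900 at 0.02 and 1160 at 0.05. Once ICC exceeds 58/5000 = 0.0116, no number of extra patients in these practices restores the sensitivity of 5000 independent ones. At ICC 0.02 with unlimited patients, the detectable difference is still 2.802 × √(2/(2900/3)) = 0.127 SD.

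**Merged and unequal clusters.** The article gives neither the merged count nor the spread of sizes, so this is illustration only. With 39 clusters (m = 128.2), a coefficient of variation of size of 0.5 and ICC 0.02, DE = 1 + ((1 + 0.5²) × 128.2 − 1) × 0.02 = 4.19. Effective N is then 1195, the detectable difference 0.199 SD and power at 0.20 SD about 81%. Merging and unequal sizes both move the result in the unfavourable direction.

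**The case against.** The strongest reply is that the section claims nothing precise. It concedes that no formal power analysis was done, labels its premises as assumptions, and attaches no power or difference to the 5000. The 0.097 SD reference point is therefore this review's, not the plan's. That stands, and it is why the claim is called unsupported rather than numerically wrong. It does not excuse the step from unknown to absent.

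Other points that stand in part:

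- The ICC range is assumed. The more than twofold loss appears only near 0.05; at 0.01 to 0.02 the inflation is 1.4 to 1.6 times.
- The sentence on power is true as a general statement and also names clusters and repeated measures. Measurement at T0, T1 and T2, correction for baseline differences and stratification could recover precision. Dropout and unequal clusters, also left out of the main table, work the other way.
- The Discussion describes variation in care and possibly in effect, not in Katz scores. It makes a zero practice effect implausible; it does not state the opposite.
- The cited study is not shown, so whether it supports the assumption cannot be judged. The article reports no figure from it.

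Two stronger readings are tempting. One is that the trial is underpowered. The documents do not support this: no target difference is stated, and power at 0.20 SD remains high at ICC 0.01 to 0.02. The other is that the analysis will ignore clustering. Data analysis names a mixed linear model without listing its random effects, a detail an analysis plan may supply. Equally, a model that includes cluster would give honest intervals but would not make the planning claim sound.

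**Conclusion.** The concern holds as a fault in the stated justification. For any ICC above zero the section overstates what 5000 patients in at most 58 randomised units can detect. The direction needs only a positive ICC; the size depends on an ICC the article does not give. Under the listed assumptions the detectable difference rises from 0.097 SD to between 0.132 and 0.223 SD for ICC 0.01 to 0.05. Differences near 0.10 SD are clearly affected, while differences near 0.20 SD are still detected with good power unless the ICC is toward the top of the range or the clusters are markedly fewer or more unequal. This should be fixed, but the validity of the design and analysis does not depend on it.

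**What to change.** Rewrite the Sample size calculation paragraph:

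- Delete the assumption of no practice effect and the claim that 5000 patients make relevant effects detectable.
- State the number of randomised clusters after merging, per arm, with mean size and its variation.
- Give the detectable pairwise Katz difference in SD units over ICC 0.005 to 0.05, with the significance level and power used.
- Update it with the SD and ICC estimated from the T0 Katz data, pooled over arms without unblinding. These are the quantities the section says are unavailable. Keep the range alongside, because the follow-up ICC may differ from the baseline one.

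Do not change recruitment. The cost is one paragraph and one pooled variance-components run. The downside is that the stated sensitivity becomes less favourable.
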